| **Statistical Analyses** | Chi-square test will be used to evaluate the association between leaks and perfusion. Logistic regression analysis will be further utilized to evaluate covariates influencing the presence/absence of leaks, with specific attention to the predictive value of percent maximum perfusion metrics and time to maximum metrics at the set timepoints in the protocol. With leaks of any severity occurring in a minimum 20% of pancreatectomies based on extensive published data. Our projected sample size of 50 will achieve 80% power to detect at least 25% difference in leaks rate between two group assuming 20% leak rate for normal ICG perfusion group.  We plan to enroll patients on a rolling basis. With a liberal estimated exclusion of 30% due to the multiple and complex postoperative factors known to be associated with leak (hemorrhage, sustained hypotension, vasopressor requirements included in “Exclusion Criteria”) we anticipate screening 75 patients and enrolling 50. The overall study will be paused if the following events occur: Life-threatening grade 4 toxicity attributable to protocol therapy that is unmanageable, or unexpected, death suspected to be related to ICG injection, as indicated by statistical stopping rules in this protocol. |

SCHEMATIC OF STUDY DESIGN

[figure not shown]

|  | **Preop visit** | **Surgery and Postoperative Period** | | | | |
| --- | --- | --- | --- | --- | --- | --- |
| **Procedure** |  | **Day 1 (Day of Surgery)** | **Day 4±3**  **(Post-operative Day 3)** | **Day of Discharge** | **Discharge + 7-14 Days (Post-Operative Follow-up)** | **Day 30** |
| Physical exam | x | X | X | X | X |  |
| Vital signs^1^ | x | X | X | X | X |  |
| ECG (if indicated) | x | X |  |  |  |  |
| Routine blood draw^2^  (1 tablespoon) |  | X | X |  |  |  |
| Drain Fluid Analysis for amylase |  |  | X |  |  |  |
| Pregnancy test (if indicated) | x | X |  |  |  |  |
| Review any adverse events |  | X |  |  | X | X |
| Review all other medications |  | X |  |  |  |  |
| ICG |  | X |  |  |  |  |
| Pancreas Resection |  | X |  |  |  |  |

TABLE OF CONTENTS

[TABLE OF CONTENTS 7](#_Toc1924134513)

[LIST OF TABLES 7](#_Toc453567276)

[LIST OF FIGURES 7](#_Toc1478094859)

[LIST OF ABBREVIATIONS 7](#_Toc1089401493)

[0. BACKGROUND INFORMATION AND SCIENTIFIC RATIONALE 9](#_Toc2112760570)

[0.0 Background 9](#_Toc1747993032)

[0.0.0 Overview of study disease(s) 9](#_Toc2072564894)

[0.0.1 Overview study intervention(s) 10](#_Toc2069882099)

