# BACKGROUND INFORMATION AND SCIENTIFIC RATIONALE

## Background

[figure not shown]

Cancer of the pancreas will cause more than 50,000 deaths this 2023 in the US alone. The incidence of pancreatic cancer has been growing by 1% a year for the last two decades.^1^Pancreatic cancer has one of the lowest overall 5-year survival rates of all organ tumors, with 5-year-survival rates estimated at around 10%. 5-year survival rates can increase to more than 30% when tumor and patient characteristics allow for resection.^2^ Open pancreaticoduodenectomy and distal pancreatectomy are the treatment of choice when tumors are limited to the pancreas. These surgical procedures have high rates of morbidity, with the most serious complication being pancreatic leaks. It is estimated that up to 30% of all patients that undergo removal of the pancreas develop a pancreatic leak. Typically, undetectable at time of surgery, pancreatic leaks occur at the pancreas to bowel anastomosis (fig 1a, yellow arrow). Diagnosis is done when clinical suspicion is high and entails measurement and analysis of suction drains (fig 1b). Pancreatic leaks prolong postoperative hospital length of stay, delay initiation of chemotherapy and increase risk for infection.^3^ Because adequate recovery is hindered by pancreatic leaks, minimizing the risk for this complication is of uttermost importance for improving patient outcomes. Recent studies have analyzed different methods to predict the risk for developing a pancreatic leak after pancreatectomy with variable success. However, these methods involve postoperative measurements. ^4, 5^ Because it arises from dual embryologic sources, the surgical neck of the pancreas is a poorly perfused watershed region of the gland, subject to hypoperfusion.^6, 7^ Ischemia of the pancreatic remnant is a factor for the development of leaks.^8-10^ Currently, surgeons rely on direct visualization of pancreatic tissue and ultrasound to estimate optimal blood flow. Present methods have been of limiting value in predicting adequate blood flow in both open pancreaticoduodenectomy and distal pancreatectomy.^11-12^ An improved intraoperative technique to analyze blood perfusion could guide surgical margins to minimize risk for pancreatic leaks. Indocyanine green (ICG) fluorescence is a method widely used to assess blood perfusion of tissues during surgery. ICG use is described in recent literature of pancreatectomy.^13-15^ However, there is no prospective systematic analysis of its use in assessing the risk of developing a pancreatic leak.

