# STATISTICAL CONSIDERATIONS

## Statistical Hypothesis

This is an open label, one arm phase II study to assess the diagnostic perfusion characteristics by intraoperative ICG injection on pancreatic leak rates. It is hypothesized that remnant pancreatic gland perfusion will be readily and objectively evaluated and that hypoperfusion will be associated with increased rates of pancreatic leaks postoperatively.

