## Sample Size Determination

This primary objective of study is to detect the difference in leak rates between normal and reduced ICG perfusion group. Since there are no existing data of ICG perfusion in the pancreas, the sample size calculation was not based on the hypothesis but we provided the detectable difference between two groups. Anticipating the balanced number between two groups, our sample size of 50 will have 80% power to detect at least 25% difference in leaks rate between two group assuming 20% leak rate for normal ICG perfusion group.

We consider a liberal exclusion of 30% due to multiple and complex postoperative factors known to be associated with leaks. We anticipate screening 75 patients and enrolling 50.

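### The sizing gives the normal-perfusion group the protocol's all-patient minimum leak rate (20%) with no basis of its own, and 80% power for a 25-point difference is not reached at any leak rate the protocol cites

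*Protocol*

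**What the plan says.** Protocol 10.1 (Sample Size Determination) states that "our sample size of 50 will have 80% power to detect at least 25% difference in leaks rate between two group". The base rate behind that figure is set in the same sentence by the words "assuming 20% leak rate for normal ICG perfusion group". Equal group sizes are a further condition: "Anticipating the balanced number between two groups". The section also says that no ICG perfusion data exist for the pancreas, so that it reports a detectable difference instead of sizing on a hypothesis.

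The Synopsis (Statistical Analyses) repeats the power sentence. Immediately before it stands "With leaks of any severity occurring in a minimum 20% of pancreatectomies based on extensive published data". The Background (0.0) gives the other all-patient figure: "It is estimated that up to 30% of all patients that undergo removal of the pancreas develop a pancreatic leak".

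Section 10.0 (Statistical Hypothesis) expects that "hypoperfusion will be associated with increased rates of pancreatic leaks postoperatively". The test is a chi-square test at 0.05 (10.3.0 and 10.3.1). The design is a single arm of 50 patients, classified by their own ICG result at a 60% cutoff (2.0).

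**The concern.** The two perfusion groups are not arms with rates that can be set freely. They are the two parts of one cohort, so their leak rates, weighted by group size, must average to the cohort's rate. If reduced perfusion raises leaks, as section 10.0 expects, the normal group must lie below the cohort rate. Giving the all-patient figure to the normal group therefore commits the sizing to a cohort rate above that figure, and the protocol neither states nor supports that rate.

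This is separate from whether the power figure is right. A sponsor who corrects only the power and keeps the 20% base moves the implied cohort rate further from the rates the protocol cites. The detectable difference is the protocol's only sizing statement, so readers will rely on it when they judge what 50 patients can show.

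**Working it through.** **Inputs.** N = 50 in balanced groups, hence 25 v 25 (10.1). Normal-group rate 20% and difference 25 points (10.1); the other group is at 45%, given the direction in 10.0. Chi-square test at 0.05 (10.3). Sidedness is not stated; two-sided is assumed. Overall leak rate: minimum 20% (Synopsis), up to 30% (Background).

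**1. The plan's own figure.** Normal approximation with pooled variance under the null:

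- average rate = (0.20 + 0.45)/2 = 0.325
- null SE = √(2 × 0.325 × 0.675/25) = 0.1325
- alternative SE = √((0.20 × 0.80 + 0.45 × 0.55)/25) = 0.1277
- power = Φ((0.25 − 1.96 × 0.1325)/0.1277) = Φ(−0.08) = 0.47

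Exact enumeration of the uncorrected Pearson test over all 26 × 26 tables gives 0.49; Yates and Fisher give 0.36. A one-sided test gives 0.60 (normal approximation). Even 50 per group gives only 0.77. The stated 80% is not reproduced; two-sided it needs 54 per group.

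**2. Implied cohort rate.** With a share f of patients in the reduced-perfusion group, overall rate = 0.20 + 0.25f.

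| f | Overall rate | Leaks in 50 |
|---|---|---|
| 0.5 | 32.5% | 16.25 |
| 0.4 | 30% | 15 |
| 0.2 | 25% | 12.5 |

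The protocol's figures correspond to 10 leaks (20%) and 15 leaks (30%).

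**3. Normal group held at 20%, cohort rate held at a cited value.** Under balance, the reduced group = 2 × overall − 20%. Exact Pearson rejection rates:

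- 20% overall (20% v 20%, no difference): 5.5%
- 25% overall (20% v 30%): 13.5%
- 30% overall (20% v 40%): 35%

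**4. Gap of 25 points kept, cohort rate held at a cited value.** Groups at overall ± 12.5 points, exact Pearson power:

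- 20% overall (7.5% v 32.5%): 65%
- 25% overall (12.5% v 37.5%): 56%
- 30% overall (17.5% v 42.5%): 51%

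**5. Difference that does reach 80% power**, exact Pearson, 25 v 25:

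| Anchor | Group rates | Difference | Overall |
|---|---|---|---|
| Normal group 20% | 20% v 56.5% | 36.5 points | 38% (about 19 leaks) |
| Overall 20% | 5% v 35% | 29 points | 20% |
| Overall 25% | 9% v 41% | 32 points | 25% |
| Overall 30% | 13% v 47% | 35 points | 30% |

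**The case against.** A reader might infer that this cohort cannot show 20% v 45%, or that the 20% input is an error in itself. The documents support neither reading, for these reasons:

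- The 20% is written as a minimum, so a 32.5% cohort rate does not contradict the Synopsis.
- The only upper figure, up to 30%, is not said to count biochemical leaks, which the primary endpoint does count (1.0). The same Background paragraph describes diagnosis on clinical suspicion, whereas section 7.1 takes amylase from all surgical drains. This cohort's rate may therefore be higher than 30%.
- The excess over 30% is 16.25 − 15 = 1.25 leaks. At a true rate of 30%, 16 or more leaks in 50 occur with probability 43%.
- The excess depends on the equal split, which the protocol only anticipates. At 40% or fewer hypoperfused, 20% v 45% fits within 30%.
- That the 20% was carried over from the all-patient figure is inferred from adjacency and from the absence of any other source. The protocol does not say so.
- The 20% base does not cause the power shortfall. Lower base rates raise power for the same gap (step 4).

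All six stand, and they limit the point to an assumption without support. They do not rescue the power statement: none of the cited overall rates brings a 25-point difference to 80%. Nor do they remove the need to state the implied cohort rate, because the corrected difference from a 20% base implies about 38%. Even with 40% hypoperfused, 20% v 56.5% implies 0.6 × 20 + 0.4 × 56.5 = 34.6%.

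It is also fair to say that group rates placed symmetrically around the cohort rate are themselves an assumption, and that the protocol does not support a 5% normal-group rate either. The suggested wording therefore has to present them as illustrations of what is detectable, not as expected rates.

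**Conclusion.** The point holds as a limited correction. The sizing assigns the protocol's minimum all-patient leak rate to the lower-risk group with no separate source. Under its own balance assumption it thereby implies 32.5% overall, about one leak in 50 more than the highest rate it cites. That is possible but unsupported. The larger fault in the same sentence is that 80% power for 25 points is not delivered: exact power is 49% as stated, and 51% to 65% at overall rates of 30% to 20%. The two should be corrected together, because mending the power alone gives about 36.5 points and an implied 38% overall.

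These figures assume 25 v 25, a two-sided 0.05 level and the uncorrected Pearson test. By the normal approximation, a one-sided test would still fall short: 60% as stated, and 72% at the most favourable cited rate (20% overall). The range of 20% to 30% joins a floor and a ceiling that may be defined differently, so it shows what the protocol cites and does not forecast this cohort's rate.

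**What to change.** In section 10.1 and in the Synopsis (Statistical Analyses), restate the detectable difference together with the overall leak rate it implies. Suggested wording: *With 25 patients per group and an overall leak rate of 20% to 30%, a two-sided chi-square test at 0.05 has 80% power for a difference of about 29 to 35 percentage points (for illustration, about 5% v 35% to 13% v 47%).*

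If the sponsor prefers to keep 20% for the normal-perfusion group, give its basis and state a detectable difference of about 36 to 37 points with the implied overall rate of about 38%.

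The cost is two restated sentences, with no change to the sample size or the analysis. The downside is that the stated detectable difference becomes less favourable than 25 points.

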# STUDY DESIGN

## Description of the Study Design

*Refer to* Section 11*, Statistical Analysis for additional information regarding statistical methods used in this study.*

This is a Phase II study to assess diagnostic parameters of hypoperfused pancreatic cut edge via ICG and its relation to fistula formation versus conventional measurements. The study design consists of a single arm intervention group (n=50).

The trial will commence with the enrollment of the fifteen patients, after these 15 casesa logistics run-in of the OR ICG technique and timing will be done. During the logistics run-in, the PI will evaluate team satisfaction and measurement outcomes. This will be done through the application of a 3-question paper-based quality survey, attached in the supporting documents for the protocol. If an average score below 50% is given, study will be terminated to avoid negative impact on the logistics of pancreatectomies. Survey scores are calculated depending on the answer given, A= 0% B = 16.5% C = 33%. Minimum score 0 maximum score 100. Progressive study enrollment will continue throughout the adjustments, and enrollment will be halted if any major concerns arise. If the interim analysis does not result in study termination, enrollment of the remaining participants will resume to enroll a total of 50 patients completing study intervention and follow-up.

Aside from interim analysis evaluating logistics. A patient safety analysis will be performed at the same time. Herein, potential factors of the clinical trial that could negatively impact patient outcomes will be addressed. These factors include adverse effects of ICG administration and factors from the clinical trial process that negatively impact the conventional treatment course of patients. If any concerns are identified on interim safety analysis, the study could temporarily pause enrollment until the issues are addressed. This is to supplement study stopping rules delineated in 9.6 and Data and Safety forms.

The study schedule will be divided into 2 periods: (1) the intra-surgical period which starts at the time of ICG injection and ends when the surgical procedure is terminated and (2) the postoperative period which begins at the end of surgery and ends 30 days postoperatively.

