## Enrollment Procedures

This is a Phase II trial, and there is no randomization for treatment.

- - 1. Enrollment Procedures for the OHSU Site

Eligibility must be confirmed and documented by the Principal Investigator prior to enrollment.

Materials required to complete the eligibility review include, at minimum:

• Current IRB-approved consent form and HIPAA Authorization for the study signed & dated by the participant

• Documented (signed and dated) attestation by the PI confirming participant’s eligibility based on available source documentation and authorizing enrollment

• Direct surgical evaluation at the time of planned study intervention to verify anatomic eligibility for ICG injection

Once eligibility is confirmed, the participant is considered ‘enrolled’ once study intervention is performed.

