## Participant Discontinuation or Withdrawal

Participants are free to withdraw consent and discontinue participation in the study at any time and without prejudice to further treatment. If a participant no longer wants to receive investigational product, but is willing to come for follow-up appointments, the participant’s request should be honored, if possible.

If a participant withdraws consent, they should be asked to specify if they are withdrawing consent to all further participation in the study, including any further follow up (e.g., survival contact telephone calls) or if they are choosing to withdraw only from further study intervention, meaning that further follow-up and data collection about their disease and health status is allowable. The participant should also be asked about their consent to the future use of their study-generated data and any biological samples, as applicable.

No further participant contact should be made if the participant withdraws consent for participation in the study. Information about the reason(s) for discontinuation and collection of any new or ongoing AEs should be collected at the time the participant withdraws consent.

A participant may also be withdrawn from the study by the Sponsor/Sponsor-Investigator, Investigator, local IRB, or regulatory authorities.

Reasons for a participant to discontinue the study may include the following:

• Participant dies or is lost to follow-up

• Participant withdraws consent for any further participation

• The end of study is reached

• Pregnancy

• Significant study intervention non-compliance

• If any clinical adverse event (AE), laboratory abnormality, or other medical condition or situation occurs such that continued participation in the study would not be in the best interest of the participant

• Disease progression which requires discontinuation of the study intervention

• If the participant meets an exclusion criterion (either newly developed or not previously recognized) that precludes further study participation

In the event of a pregnancy, the study treatment will not be administered. Refer to Section 10.6.5 regarding reporting of pregnancy. Participants who withdraw or discontinue after receiving study intervention count towards the enrollment total.

- - 1. Handling Participant Discontinuation from Study

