## Early Termination or End of Treatment Visit

Any participant who undergoes early termination will undergo end of study visits depending on their progress in the protocol. Participants who have not received ICG injection are not considered enrolled, will not require a follow up visit and will be treated per standard of care. Participants undergoing termination following pancreatectomy will have an end of study visit at the time of their regular post-op visit and will be cared for per the standard of care.

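### The 30% postoperative loss is placed before enrolment although enrolment occurs at ICG injection, so the number given ICG and the number analysed are not fixed

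*Protocol*

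**What the plan says.** Section 10.1 (Sample Size Determination) states "We consider a liberal exclusion of 30% due to multiple and complex postoperative factors known to be associated with leaks" and continues "We anticipate screening 75 patients and enrolling 50". The synopsis, under Statistical Analyses, gives the same allowance, "With a liberal estimated exclusion of 30% due to the multiple and complex postoperative factors known to be associated with leak", with hemorrhage, sustained hypotension and vasopressor requirement as examples. It gives the number of participants as 50.

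Enrolment is defined elsewhere:

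- Section 4.0 (Consent and Screening) ends the screening period when the ICG injection starts.
- Section 4.1 (Enrollment Procedures): "Once eligibility is confirmed, the participant is considered ‘enrolled’ once study intervention is performed".
- Section 7.5 (Early Termination or End of Treatment Visit): "Participants who have not received ICG injection are not considered enrolled".
- Section 4.3 (Screen Failures) limits screen failures to consented patients who are ineligible or who leave before study treatment.
- Section 4.4 (Participant Discontinuation or Withdrawal) lists a newly developed exclusion criterion as a reason to discontinue, and adds "Participants who withdraw or discontinue after receiving study intervention count towards the enrollment total".

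Three further places bear on the count. Section 3.1, criterion 4, excludes patients for events tied to postoperative days 3-5 and for transfusion during or after surgery. Section 2.0 says accrual goes on to "enroll a total of 50 patients completing study intervention and follow-up". Section 10.2 defines the efficacy evaluable population as enrolled patients who had the resection, received ICG and had up to 30 days of follow-up; it does not mention criterion 4.

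**The concern.** The 30% is described as a loss from postoperative events but is used as a screening loss. Under sections 4.1 and 4.4, a patient with such an event has already received ICG and is one of the 50. The 75-to-50 step therefore describes a loss that cannot occur at that point.

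The count of 50 has two incompatible meanings: 50 given ICG (synopsis, 4.1, 4.4, 10.1) or 50 who complete intervention and follow-up (2.0). With any loss after ICG, both cannot hold.

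Three things depend on the answer: how many patients are exposed to the study drug, when accrual stops, and how many patients enter the primary comparison. The power statement in 10.1 uses 50 as though none were lost.

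**Working it through.** **Inputs.** From 10.1 and the synopsis: 75 screened, 50 enrolled, 30% exclusion, 20% leak rate with normal perfusion, 25-point difference (so 20% v 45%), balanced groups. From 10.3: chi-square test at 0.05. Sidedness is not stated; two-sided is assumed.

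**The plan's own step.** 75 x 0.70 = 52.5 and 50/0.70 = 71.4. The ratio 50/75 is a loss of 33%. So 75 to 50 is roughly a 30% loss with rounding up. The arithmetic is acceptable; the stage at which the loss is placed is not.

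**Order of events under the protocol's definitions.** Consent and screening, then ICG (enrolment), then end of surgery, then postoperative events (criterion 4). Losses before ICG are screen failures and do not count in the 50. Losses after ICG do count.

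**How much of the 30% falls after ICG.** The protocol does not say. Some listed events are intraoperative and could precede ICG, so losses of 10%, 20% and 30% are shown as an assumed range.

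**Formulas.** With loss d: analysable = 50 x (1 - d); given ICG to keep 50 evaluable = 50/(1 - d), rounded up. Power with n per group and mean proportion 0.325:

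z = (0.25 - 1.96 x s0)/s1, where s0 = sqrt(2 x 0.325 x 0.675/n) and s1 = sqrt((0.20 x 0.80 + 0.45 x 0.55)/n); power = Φ(z).

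- N = 50 (n = 25): s0 = 0.1325, s1 = 0.1277, z = -0.076, power 47%.
- N = 35 (n = 17.5): s0 = 0.1583, s1 = 0.1526, z = -0.395, power 35%.

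The detectable difference is the increase over 20% at which the same formula, with the mean proportion updated, gives 80% power.

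| Loss after ICG | Analysable if 50 enrolled | Power, 20% v 45% | Detectable difference at 80% power | Given ICG if 50 must be evaluable | Left of 75 for screen failures |
| --- | --- | --- | --- | --- | --- |
| 0% | 50 | 47% | 38 points | 50 | 25 |
| 10% | 45 | 43% | 40 points | 56 | 19 |
| 20% | 40 | 39% | 42 points | 63 | 12 |
| 30% | 35 | 35% | 45 points | 72 | 3 |

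Exact enumeration of the uncorrected chi-square test gives 49% at 25 per group and 34% at 18 and 17, so the approximation is adequate.

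At 72 given ICG, exposure is 44% above the stated 50 (72/50 = 1.44).

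**The case against.** The strongest reply is that the intention can be read from section 2.0: accrue until 50 complete. The figure of 75 fits this, since 71.4 rounds up towards it, and the terms for screening and enrolment in 10.1 would then be used loosely. This has weight, and on this reading 50 is the analysed number. But then up to about 72 patients receive ICG, which neither the synopsis nor 10.1 says, and the rule in 4.4 would stop accrual too early.

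A reader might infer that as few as 35 patients will be analysed. The documents do not support this as a forecast, for three reasons:

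- The protocol calls the 30% liberal, and some listed events (hemorrhage, intraoperative transfusion) can precede ICG, which section 5.0 places just before reconstruction or before closure. Patients lost at that stage would be true screen failures.
- The efficacy population in 10.2 does not remove patients who meet criterion 4. If 10.2 governs, 50 enrolled stays close to 50 analysed, but then the 30% allowance has no function.
- Section 2.0 favours 50 completers.

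So 35 is the lower end of this range. A reader might also blame this point for the whole fall from 80% to 35% power. Most of that fall is a different error: with all 50 analysed, power is already about 47%.

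**Conclusion.** The inconsistency stands. As the protocol defines enrolment, a postoperative loss cannot lie between screening and enrolment, and sections 2.0, 3.1, 4.1, 4.4, 10.1 and 10.2 do not agree on what the 50 are. Depending on which section staff follow, and for a post-ICG loss of 10% to 30%, either 45 to 35 patients are analysed or 56 to 72 receive ICG.

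The power attributable to this point is at most the step from 47% to 35%; the detectable difference moves from about 38 to about 45 points. These figures rest on a two-sided 0.05 test, equal groups, and application of criterion 4 to the analysis.

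Cases dropped for failed blinding (4.2) or missing essential data (10.4) would reduce the analysed number further; neither has a separate allowance. This needs correction before the sample size can be relied on.

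**What to change.** Use one definition of enrolled and one of evaluable in the synopsis and in sections 2.0, 3.1, 4.1, 4.4, 10.1 and 10.2. In 10.2, say whether patients who meet criterion 4 after ICG remain in the efficacy population. In 10.1 and the synopsis, give both the number who will receive ICG and the number expected in the analysis, describe the 30% as loss after enrolment, and quote power and detectable difference for the number analysed. Report the 80% power error at N=50 separately.

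This is a change of text and restated, less favourable figures. It needs no extra patients if 50 given ICG is kept as the target. If 50 evaluable is kept, the larger exposure must be stated and approved. Removing the postoperative exclusions would also narrow the gap, but that is a design decision for the sponsor, needs an approved amendment, and is not required for this correction.
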